# Effect of Tai Chi combined with Kinesio taping on posture control of football players with FAI: protocol for a randomized controlled trial

**DOI:** 10.1186/s13063-022-06083-5

**Published:** 2022-02-19

**Keywords:** Functional ankle instability, Tai Chi, Kinesio taping, Posture control, Ankle joint, Balance

## Abstract

**Background:**

Functional ankle instability (FAI) of college football players is an important risk factor affecting their training and competition. Physical therapy and appropriate sports intervention can improve the stability of FAI patients. Previous studies have shown that Tai Chi (TC) and Kinesio taping (KT) can improve the posture control ability of FAI patients. However, whether Tai Chi combined with Kinesio taping effect patch can be used as an effective exercise for rehabilitation of college football players with FAI is not yet proven.

**Methods/design:**

Fifty-three FAI college football players were randomly assigned to 3 groups: TC+KT (*n* = 20); TC+KTp (placebo Kinesio taping, KTp, placebo) (*n* = 17), and KT (*n* = 16). The TC+KT group received TC and KT functional correction technical intervention, the TC+KTp group received TC and placebo KT technical intervention, and the KT group received KT functional correction technical intervention. Each of the three groups received 30 min each time, 3 times a week, for a total of 6 weeks of intervention training. Star Excursion Balance Test (SEBT) and UniPedal Stance Test (UST) at baseline (before), 4 weeks after intervention (middle), and 6 weeks after intervention (after) and Toe Touch Test (TTT) were evaluated.

**Discussion:**

For the first time in this trial, the impact will be evaluated. If the results are the same as expected, they will provide evidence that Tai Chi combined with Kinesio taping sticking intervention can promote the posture control of college football players with FAI.

**Trial registration:**

Chinese Clinical Trial Registry ChiCTR1900027253. Registered on 6 November 2019.

**Supplementary Information:**

The online version contains supplementary material available at 10.1186/s13063-022-06083-5.

## Background

Football is the world’s most popular sport. It has the characteristics of fighting fierce, repeated kicks, rapid changes of direction, instant acceleration, instant jumping, and landing. These features make it one of the sports with the highest incidence of sports injuries [1]. Much higher than basketball and handball [2]. Football injuries are mainly concentrated in the lower limbs [3], especially the ankle joints [4, 5], which account for about 85% of the total football injuries [6]. Due to the incomplete rehabilitation or overuse of the football player’s ankle joints, it is easy to cause repeated injuries. It is the highest risk of recurrence in football injuries, reaching 80% [7]. Over time, functional ankle instability (FAI) will gradually develop. At present, there is no expert consensus on the mechanism of FAI. Relevant studies have shown that it is related to the loss of proprioceptive sensitivity [8, 9], loss of strength [10], and weakened sense of balance after ankle joint injury [11].

To ensure the proper training and competition of FAI university football players, effective rehabilitation is still a difficult problem to solve in a short time. At present, international research on rehabilitation of FAI mainly focuses on its plyometrics and balance training [12], proprioception [13], strength [14, 15], balance training [16], strength and proprioception intervention [17], and motor sensory training [18]. To a certain extent, reduce the recurrence rate of ankle sprains.

In addition to exercise therapy, other strategies for FAI intervention are also suggested to improve the flexibility and stability of the ankle joint. For example, KT improves the vertical jump effect of FAI [19]; KT improves the functional performance of female basketball players with unstable ankle joints [20]. And KT improves the dynamic balance of FAI [21]. Studies have shown that KT can also increase muscle strength [22], enhance proprioception [23], and improve flexibility [24]. However, international studies have observed the effects of control, nonelastic adhesive tape and KT subjects on the neuromuscular performance of femoral quadriceps, postural balance, and lower limb function, and the results show that there is no significant alteration in the effects of KT and control and nonelastic adhesive tape [25]. By observing the effect of KT on static postural control in FAI patients at different time points, the results showed that KT cannot achieve a significant improvement effect [26]. At present, although most studies have proved the positive effects of KT, no scientific consensus has been formed, and more research is needed to promote the consistency of KT's effects.

Tai Chi is a sports event with the main feature of single-leg support of the lower limbs. It has been widely used in the promotion of human health. The role of posture control is mainly manifested in improving the proprioception of the elderly [27], keeping balance [28] and preventing falls [29] and knee osteoarthritis [30] In other aspects, there are few studies on Tai Chi’s intervention in FAI, especially the intervention of college football players in FAI. There is insufficient evidence to prove the intervention effect of Tai Chi or combined Kinesio taping effect on the posture control such as stability and flexibility of college football players with FAI. This trial uses a rigorously designed randomized controlled trial to evaluate the influence of Tai Chi intervention or combined intervention with KT on the posture control of football players with FAI. It can provide a scientific theoretical basis for the promotion of Tai Chi, provide new rehabilitation methods for rehabilitation therapists, and reduce the treatment cost of FAI rehabilitation.

## Methods/design

### Study purpose

The purpose of this trial is to evaluate the effectiveness of a 6-week Tai Chi or combined Kinesio taping intervention on the posture control of college football players with FAI.

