### Study design

This article is a double-blind randomized controlled trial, recruiting 66 eligible college football players with FAI, randomly divided into 3 groups: TC+KT group, TC+KTp group, and KT group; the ratio is 1:1:1. Participants in the TC+KT group will receive 6 weeks of Tai Chi (3 times a week, 30 min each time) combined with Kinesio taping effect patch intervention; the TC+KTp group will receive 6 weeks of Tai Chi and muscle placebo technical intervention with internal effect patch; and the KT group will receive 6-week Kinesio taping effect patch intervention. Measurements will be taken at the baseline, mid-intervention period (4 weeks), and late intervention period (6 weeks) to check the maintenance of any intervention effects. The participant flow for this trial is presented in Fig. 1. The present protocol follows the Standard Protocol Items: Recommendations for Interventional Trials (SPIRIT) guidelines and fulfills the SPIRIT checklist (see Additional file 1).

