### Intervention

#### Intervention plan

The three different interventions lasted for 6 weeks. During this period, they normally participated in the usual football courses (i.e., 2 times a week, 90 min each time, 1 game on weekends). Subjects in the TC+ KT and KT groups, in both ankles, had KT functional correction taping technology. The KTp+ TC group used placebo technology (tension-free) KT. The TC training of subjects in the TC+ KT and KTp+ TC groups focused on lower limb posture control.

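### The purpose and planned conclusion speak of the effectiveness of Tai Chi and of the combination, but with no arm free of both treatments the design measures two add-on effects and one head-to-head

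*Protocol article*

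**What the plan says.** The Study purpose section of the protocol article says that the trial will "evaluate the effectiveness of a 6-week Tai Chi or combined Kinesio taping intervention on the posture control" of college football players with functional ankle instability. It names no comparator. The end of the Background and the Discussion repeat the aim in similar terms. In the abstract, the Discussion paragraph says of the results, should they turn out as expected, that "they will provide evidence that Tai Chi combined with Kinesio taping sticking intervention can promote the posture control" of these players.

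The Study design section has participants "randomly divided into 3 groups: TC+KT group, TC+KTp group, and KT group", in equal ratio. The Intervention plan fixes what each arm gets: "Subjects in the TC+ KT and KT groups, in both ankles, had KT functional correction taping technology", while "The KTp+ TC group used placebo technology (tension-free) KT". Tai Chi is given in TC+KT and TC+KTp. For the third arm, Study design says that "the KT group will receive 6-week Kinesio taping effect patch intervention" and mentions no Tai Chi. All arms continue their usual football classes and weekend game.

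The Statistical analysis section plans a mixed analysis of variance with group and time as factors, followed by Bonferroni-corrected post hoc comparisons. It does not say which comparison answers the purpose. On what tape does by itself, the Background says that "no scientific consensus has been formed, and more research is needed".

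**The concern.** Effectiveness is always relative to something. Read plainly, the purpose asks whether Tai Chi works and whether Tai Chi plus tape works. The arms fill three cells of a two-by-two layout (Tai Chi yes or no, active tape yes or no), and the empty cell is the one with neither treatment. That cell is what both questions would be measured against.

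Two misreadings are then possible when results are reported. First, TC+KTp v KT is the only comparison in which Tai Chi appears without active tape, so it may be taken as the stand-alone Tai Chi result, although both components change between those arms. Second, because time is a factor in the analysis, improvement from baseline to week 6 within TC+KT may be taken as proof that the combination promotes posture control.

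**Working it through.** **Inputs.** Arm contents come from the Study design, Intervention plan and Placebo Kinesio taping sections. The plan gives no figure for any of these contrasts, so there is none to reproduce. The stated sample size (54, raised to 66) does not enter the argument.

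**Step 1: arm means.** Let m be the mean with neither active treatment, t the effect of Tai Chi against neither, k the effect of active tape against neither, and i their interaction.

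| Arm | Tai Chi | Active tape | Mean |
|---|---|---|---|
| TC+KT | yes | yes | m + t + k + i |
| TC+KTp | yes | no (placebo tape) | m + t |
| KT | no | yes | m + k |
| (absent) | no | no | m |

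**Step 2: what the arms give.**

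- TC+KT − KT = t + i: Tai Chi added to active tape.
- TC+KT − TC+KTp = k + i: tape tension added to Tai Chi.
- TC+KTp − KT = t − k = (t + i) − (k + i): the head-to-head, which is the difference of the first two.

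Three means give two independent contrasts. A rank check on the coded arm means, with no assumption about i, confirmed that these three differences are estimable. Tai Chi against neither (t), tape against neither (k), the combination against neither (t + k + i) and the interaction (i) are not.

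**Step 3: what additivity would buy.** If i = 0 is assumed, the two add-on contrasts equal t and k, and their sum is the combination against neither. Without that assumption their sum is t + k + 2i, which differs from the combination effect t + k + i by exactly i. Testing i needs the absent cell.

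**Step 4: size, by illustration.** The protocol gives no values for t, k or i, so these are assumed. Suppose both add-on contrasts are 0.5 SD, so that the head-to-head is 0. Then Tai Chi against neither is 0.5 − i, tape against neither is 0.5 − i, and the combination against neither is 0.5 + 0.5 − i = 1.0 − i.

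| Assumed i (SD) | Tai Chi v neither | Tape v neither | Combination v neither |
|---|---|---|---|
| −0.5 | 1.0 | 1.0 | 1.5 |
| 0 | 0.5 | 0.5 | 1.0 |
| 0.5 | 0 | 0 | 0.5 |

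All three rows produce the same three arm differences, so the trial cannot tell them apart.

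**Step 5: change over time.** The outcomes are measured at baseline, week 4 and week 6, each time with repeated attempts, and the players keep up football throughout. Within-arm change therefore contains a practice and training component that cannot be separated from treatment without a comparator. It does not stand in for the missing cell.

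**The case against.** **The head-to-head is a legitimate randomised comparison.** This stands. A reader might infer that TC+KTp v KT is uninterpretable and should be dropped from inference. It is not: it validly shows which of two active packages does better. Removing it would also discard the only inferential comparison with Tai Chi without active tape.

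**Masking examples are resolved by the other two contrasts.** This also stands. With additive effects of t = k = 0.5 SD the head-to-head is 0, but both add-on contrasts show 0.5. With t = 0.5 and k = 0.25 it shows 0.25, while the add-on contrasts show 0.5 and 0.25. With t = 0 and k = −0.2 it shows 0.2, while they show 0 and −0.2. Ambiguity arises only if the head-to-head is read alone, and the article does not say that it will be. The real limit is the untestable interaction.

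**The article gives reasons to expect little from tape.** The Discussion cites no significant effect of four weeks of taping on dynamic and static balance in college football players, and none on the Star Excursion Balance Test. If k were truly 0, KT would serve as a reference close to no treatment. But lack of significance is not evidence of zero. The same section reports a flexibility benefit and significant short-term effects, and the Background calls the question unsettled. Taking k = 0 remains an assumption.

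**The abstract's conclusion is conditional and claims neither superiority to no treatment nor synergy.** True. Moreover, if TC+KT beat both other arms, a combination no better than neither would require both components to do harm when used alone: t = (t + k + i) − (k + i) and k = (t + k + i) − (t + i) would both be negative. That makes the qualitative conclusion plausible, but its size stays unmeasured.

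**Choice of contrasts may be left to an analysis plan.** Agreed. For the same reason, a reader should not infer that the head-to-head costs alpha (0.05/3 = 0.0167 instead of 0.05/2 = 0.025 per pair), because the article does not list the pairs. The purpose and the arms, however, are fixed here, and an analysis plan cannot create the absent comparator.

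**Conclusion.** The point holds as a mismatch between the stated purpose and planned conclusion on one side and the arms on the other. The design validly estimates Tai Chi added to active tape, tape tension added to Tai Chi, and a head-to-head that cannot attribute a difference to one component. It does not estimate Tai Chi alone or the combination against neither treatment, nor any interaction. Those effects are recoverable only under additivity, and the error in the combination effect is then the whole of the interaction, whose size the documents do not allow one to bound.

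This result depends only on the arm contents, not on any assumed effect size. It does not make the randomised contrasts invalid and does not bear on the sample size.

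**What to change.** Restate the Study purpose, and the matching sentences in the Background and Discussion, as two questions: does Tai Chi improve posture control when added to active taping (TC+KT v KT), and does tape tension improve it when added to Tai Chi (TC+KT v TC+KTp)? Reword the abstract's planned conclusion to match, and base it on those between-group contrasts, not on change over time within an arm. Keep TC+KTp v KT and label it a head-to-head of two active packages. Claim neither effectiveness against no treatment nor synergy. Date the change, and state whether group results had been seen by then.

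The cost is a narrower claim. No arm, data or players are added, and the total stays at 66. Filling the absent cell instead would, at the protocol's per-arm size, take 4 × 18 = 72 players, or 4 × 22 = 88 with its dropout allowance. With recruitment scheduled to end on 30 October 2021, that is not a practical alternative.

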### Study design

This article is a double-blind randomized controlled trial, recruiting 66 eligible college football players with FAI, randomly divided into 3 groups: TC+KT group, TC+KTp group, and KT group; the ratio is 1:1:1. Participants in the TC+KT group will receive 6 weeks of Tai Chi (3 times a week, 30 min each time) combined with Kinesio taping effect patch intervention; the TC+KTp group will receive 6 weeks of Tai Chi and muscle placebo technical intervention with internal effect patch; and the KT group will receive 6-week Kinesio taping effect patch intervention. Measurements will be taken at the baseline, mid-intervention period (4 weeks), and late intervention period (6 weeks) to check the maintenance of any intervention effects. The participant flow for this trial is presented in Fig. 1. The present protocol follows the Standard Protocol Items: Recommendations for Interventional Trials (SPIRIT) guidelines and fulfills the SPIRIT checklist (see Additional file 1).

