### Randomization, allocation, and blinding

Random grouping is carried out by individual researchers. The generation of random sequence and random list are carried out by individual researchers through the SPSS (IBM. Version 20.0) software program. This is done on subjects who have signed the “Informed Consent.” Make sure the group is hidden. Participants were randomly divided into 3 groups: TC+KT (*n* = 20), Tai Chi combined with Kinesio taping patch intervention; TC+KTp (*n* = 21), Tai Chi and Kinesio taping patch placebo technical intervention (*n* = 21); and Kinesio taping patch intervention which was performed alone.

In this trial, the assessments and treatments were performed by different therapists. The evaluator was blinded to the subject assignment. All the intervention procedures were performed by the same physiotherapist who had experience in the field of sports physical therapy. Both the physiotherapist and the participants were blinded to the purpose of the study. In addition, a different researcher, blinded to the object of the study, carried out the data analysis.

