#### Placebo Kinesio taping

The pasting of the patch is the same as before, but the tension of the patch is 0%. The patch is only attached to the subject’s ankle without any stretching. Both functional correction tape and placebo tape were applied to both ankles of the subjects, and the tape was taped once every 5 days [37]. If the subject discovers any skin allergies when changing KT, they will be excluded from the study.

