### Outcome assessment test indicators

After the subjects agreed to participate in the intervention, a preliminary assessment was made. Tests were performed before the intervention (baseline), 4 weeks later (mid-term), and 6 weeks (end of intervention). The tested variables include (1) dynamic balance, (2) static balance, and (3) flexibility.

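### The double-blind label covers all three arms, but only the evaluator is stated to be blinded to assignment, and both contrasts with the KT arm are open to the players

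*Protocol article*

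**What the plan says.** The Study design section opens with "This article is a double-blind randomized controlled trial" and attaches this to a three-arm, 1:1:1 comparison of TC+KT, TC+KTp and KT.

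The detailed account is in Randomization, allocation, and blinding:

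- Evaluator: "The evaluator was blinded to the subject assignment".
- Treating staff and players: "Both the physiotherapist and the participants were blinded to the purpose of the study".
- Analyst: "a different researcher, blinded to the object of the study, carried out the data analysis".
- Delivery: "All the intervention procedures were performed by the same physiotherapist".

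On content, Study design and Intervention plan give Tai Chi to TC+KT and TC+KTp only. The KT arm has taping, and no sham exercise is described. The Kinesio taping section sets the active tape at 70% tension. For the placebo, the Placebo Kinesio taping section says "The pasting of the patch is the same as before, but the tension of the patch is 0" (per cent).

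On timing, Study design says the measurements are taken "to check the maintenance of any intervention effects". Outcome assessment test indicators places the two post-baseline tests at "4 weeks later (mid-term), and 6 weeks (end of intervention"). Data collection lists the same three time points and no later one.

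**The concern.** Double-blind is normally read as meaning that participants and those treating them do not know the allocation. Here the players and the physiotherapist are said to be unaware only of the study's purpose, and the treatments differ in ways that they cannot miss. A reader who trusts the label would credit every contrast with protection against expectation and differential effort.

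That matters for both primary outcomes. The Star Excursion Balance Test asks for the furthest reach a player can manage, and the UniPedal Stance Test is timed until balance is lost, with a 45 s cap. Both depend on effort. A blinded evaluator protects the measurement and recording of the result, but not how hard the player tries. The contribution of Tai Chi to the combination rests on TC+KT v KT, which is one of the open contrasts.

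The maintenance wording is a smaller matter of the same kind: it invites a conclusion about lasting effect for which no off-treatment measurement is planned.

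**Working it through.** No sample size, power or error rate is involved. The check sets the sections of the protocol article side by side.

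**1. Who is stated to be blinded, and to what** (Randomization, allocation, and blinding)

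| Role | Stated to be blinded to | Is that allocation? |
|---|---|---|
| Evaluator | assignment | yes |
| Physiotherapist | purpose of the study | no |
| Players | purpose of the study | no |
| Analyst | object of the study | not as worded |

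**2. What the player can observe** (Study design, Intervention plan, Kinesio taping, Placebo Kinesio taping)

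Three arms give 3 × 2 / 2 = 3 pairwise contrasts.

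| Contrast | Tai Chi differs | Tape tension differs | Open to the player? |
|---|---|---|---|
| TC+KT v TC+KTp | no | yes, 70% v 0% | not settled |
| TC+KT v KT | yes | no, 70% in both | yes |
| TC+KTp v KT | yes | yes, 0% v 70% | yes |

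A player knows whether he practises Tai Chi. Both contrasts with KT are therefore open to the player: 2 of 3. In the remaining contrast the placebo tape is laid on the same way without stretch. Masking is possible there, but no section says that players are blinded to tape type.

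**3. What the physiotherapist can observe**

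Active tape needs a measured stretch to 70% and placebo tape none, so whoever applies it knows the type. Tape at 0% is used only in TC+KTp and identifies that arm fully. Tape at 70% narrows the arm to TC+KT or KT.

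**4. The evaluator**

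Every arm has tape on both ankles, and assessment and treatment are done by different therapists. Nothing in the article contradicts the stated blinding of the evaluator.

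**5. Follow-up after treatment**

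Follow-up after treatment = time of last visit − end of intervention = 6 weeks − 6 weeks = 0 weeks. The week 4 and week 6 tests both belong to the treatment period. They can show change on treatment from week 4 to week 6, and nothing after treatment stops.

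**The case against.** The article does not hide its arrangements. The blinding section sets out each role, and for reducing bias the Discussion relies on blinded evaluation and analysis, not on double blinding. No hypothesis, test or sample size depends on the label. The outcomes are measured distances and times with set failure or stopping rules, and the article gives no evidence on how far expectation shifts them. Tai Chi cannot readily be hidden from the people doing it. All of this stands. It limits the consequence to how the trial is described and interpreted, but it does not make the label correct.

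On maintenance, the same sentence calls week 6 the late intervention period, so the text discloses that both visits fall within treatment. If maintenance means that a week 4 effect is still present at week 6, the schedule can show it. A reader might infer that the maintenance claim is empty in every sense; the documents do not support that. What fails is the usual sense, persistence after treatment ends, and the article does not say which sense it intends.

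A reader might also infer that all players know their exact arm. That goes too far: a player in either Tai Chi arm may be unable to tell which of the two it is.

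**Conclusion.** The concern holds in limited form. The double-blind label is not supported for the trial as a whole: two of three pairwise contrasts are open to the player, the person applying tape knows its type, and only the evaluator is stated to be blinded to assignment. This rests on two readings of the article: that the KT arm has no sham exercise, since none is described, and that whoever applies the tape sets its tension. That open contrasts may be affected by expectation or effort is a judgement about effort-dependent tests; its size cannot be derived from the document.

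Two further inferences should be resisted. A reader might relabel the trial as both evaluator- and analyst-blinded, but the analyst wording is of the same kind as that used for the players and does not establish blinding to assignment. A reader might also put the visible difference between the arms at 6 weeks × 3 sessions × 30 min = 9 h of exercise. The abstract says that all three groups had 30-minute sessions three times a week, while Study design and Intervention plan give the KT arm taping only. Until these are reconciled, the 9 h figure should not be used.

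The maintenance wording is a lesser, second point: there are 0 weeks of observation after treatment.

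**What to change.** 1. In Study design, replace the double-blind label with evaluator-blinded.
2. Ask the sponsor whether the analyst is blinded to assignment and whether players are kept unaware of tape type between TC+KT and TC+KTp. Claim either only if it is confirmed.
3. State that TC+KT v KT and TC+KTp v KT are open-label for participants, and report and interpret them so.
4. Replace the maintenance wording with mid-treatment effect (week 4) and end-of-treatment effect (week 6), and draw no conclusion about persistence after treatment.
5. Reconcile the abstract's statement on sessions in all three groups with the description of the KT arm in Study design and Intervention plan.

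The cost is text only: no change to visits, sample size or tests is needed. The stated level of blinding becomes less favourable.
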